## Abstract

**Background:**

Burns and the associated wound care procedures can be extremely painful and anxiety-provoking for children. Burn injured children and adolescents are therefore at greater risk of experiencing a range of psychological reactions, in particular posttraumatic stress disorder, which can persist for months to years after the injury. Non-pharmacological intervention is critical for comprehensive pain and anxiety management and is used alongside pharmacological analgesia and anxiolysis. However, effective non-pharmacological pain and anxiety management during pediatric burn procedures is an area still needing improvement. Medical hypnosis has received support as a technique for effectively decreasing pain and anxiety levels in adults undergoing burn wound care and in children during a variety of painful medical procedures (e.g., bone marrow aspirations, lumbar punctures, voiding cystourethrograms, and post-surgical pain). Pain reduction during burn wound care procedures is linked with improved wound healing rates. To date, no randomized controlled trials have investigated the use of medical hypnosis in pediatric burn populations. Therefore this study aims to determine if medical hypnosis decreases pain, anxiety, and biological stress markers during wound care procedures; improves wound healing times; and decreases rates of traumatic stress reactions in pediatric burn patients.

**Methods/Design:**

This is a single-center, superiority, parallel-group, prospective randomized controlled trial. Children (4 to 16 years, inclusive) with acute burn injuries presenting for their first dressing application or change are randomly assigned to either the (1) intervention group (medical hypnosis) or (2) control group (standard care). A minimum of 33 participants are recruited for each treatment group. Repeated measures of pain, anxiety, stress, and wound healing are taken at every dressing change until ≥95 % wound re-epithelialization. Further data collection assesses impact on posttraumatic stress symptomatology, speed of wound healing, and parent perception of how easy the dressing change is for their child.

**Discussion:**

Study results will elucidate whether the disease process can be changed by using medical hypnosis with children to decrease pain, anxiety, and stress in the context of acute burn wounds.

**Trial registration:**

Australian New Zealand Clinical Trials Registry ACTRN12615000419561

## Background

### Global pediatric burns burden

Worldwide numbers of annual pediatric hospital admissions for burn treatment vary geographically from a rate of 4.4/100,000 total population in America (North, Central, and South) to 10.8/100,000 total population in Africa [1]. Every day in the USA approximately 300 children aged 0 to 19 years receive treatment in emergency departments for burn injuries and two children die from burns [2]. In Australia, approximately 40.1/100,000 children aged 0 to 14 years are hospitalized annually due to burns and scalds [3]. While pediatric burn mortality rates are decreasing worldwide, the morbidity attributed to burns due to factors such as pain, psychological distress, and physical impairment is increasing [4]. Thus, it is important to identify the most effective interventions to reduce the burden of burns.

### Pediatric burn pain

In modern medicine, pain has moved beyond concern as a mere disease symptom and is now considered a basic human rights issue [5]. Burns and the associated wound care procedures (e.g., wound cleaning, debridement, and dressing) can be painful for children [6]. After the initial burn is sustained, procedural pain remains both the most intense and undertreated type of pain despite continual advancements in burn wound care [6]. Furthermore, many patients indicate that wound care procedures are as painful as the original burn insult (and occasionally *more* painful), provoking intense anticipatory anxiety [7].

### Psychological distress

In addition to being painful, burn injuries can result in severe psychological distress [8]. Burn injury leads to an increased risk of children developing a range of major mental illnesses, in particular posttraumatic stress disorder (PTSD) [9, 10]. Several clinical studies have identified traumatic stress reactions in preschool children in the first year post-burn, ranging between 25 and 30 % in the acute phase to approximately 10 % one year after the burn [8]. Acute stress is prevalent in approximately one third of school-aged children post-burn, and qualitative, cross-sectional studies have identified current PTSD in 10–20 % of the children and young adults many years post-burn [8]. A prospective observational study in our burns center with 130 burn injured children found that 35 % were diagnosed with at least one psychological disorder, with a high comorbidity rate of PTSD [11]. Furthermore, prior research indicates that a clinically significant relationship may exist between symptoms of psychological distress and burn pain, each of which can exacerbate the other [12]. Unaddressed fears and anxiety contribute to noncompliance and can complicate pain management and healing [13]. Thus, treatment options that alleviate pain and distress must be offered to patients for optimal care [14].

### Physiologic effects of pain and stress on wound healing

It is worth studying endogenous pain mediators in children, not only for compassionate reasons of pain control, but also in the context of their direct physiologic effects on wound healing [15]. Widgerow theorizes that greatly increased pain mediator release in the context of burns may result in nociceptors becoming overly sensitized, increased inflammatory cellular and extracellular matrix alterations, and possibly increased hypertrophic scarring risk [15]. Hypertrophic scarring, a common thermal injury complication, is manifested by excessive collagen deposition in the healing wound bed [16]. Therefore, aside from modulating a child’s subjective (i.e., central) interpretation of pain, decreasing acute burn pain can potentially promote faster wound healing and improve long-term scar outcomes by downregulating local pain mediator release [15].

In humans the release of glucocorticoids (e.g., cortisol) and catecholamines (e.g., epinephrine and norepinephrine) elicits the classic “fight, flight, or freeze” response when psychological stress is experienced [4]. Herndon et al. have demonstrated increased levels of epinephrine and norepinephrine sustained for up to 35 weeks in children post-burn, providing evidence of the magnitude and duration of the catecholamine surge encountered in this population [17, 18]. These physiologic effects in response to stress are important, as a number of studies and meta-analyses have implicated psychological stress in significantly delaying cutaneous wound healing [19–21]. Attention to and relief of pain, anxiety, and stress for burned children is therefore a high clinical priority [13].

### Pharmacological and non-pharmacological pain and anxiety management

To prepare pediatric patients for burn wound care procedures, a pharmacological protocol is usually employed for analgesia and anxiolysis [14]. A variety of non-pharmacological techniques are also used adjunctively with pharmacological methods for pain and anxiety control. Distraction and preparation techniques and devices have demonstrated benefit in pediatric burn patients [6, 22–24]. Importantly, pain reduction during burn wound care procedures has been linked with clinically significant improvement in wound healing (i.e., re-epithelialization) rates [6, 25, 26].

### Medical hypnosis

Medical hypnosis helps patients focus their attention to lessen pain and anxiety and enhances patients’ acceptance of clinicians’ positive suggestions to change or reframe their perceptions, sensations, thoughts, and behaviors [27]. Hypnotherapeutic techniques have decreased pain and anxiety in the short term and decreased psychological distress over the long term, thereby optimizing patient outcomes and complementing existing treatment modalities [28]. Medical hypnosis can also empower pediatric patients to assist themselves at will beyond the presence of the therapist by teaching them self-hypnosis, which engenders self-mastery and active participation in their own treatment [29].

In children, clinical hypnotherapy techniques including hypnoanalgesia and hypnoanesthesia (hypnotically induced analgesia and anesthesia, respectively) have alleviated acute pain associated with a number of painful pediatric medical procedures [30]. There is a growing body of evidence supporting medical hypnosis’ ability to reduce pain and anxiety associated with venipuncture, bone marrow aspiration, and lumbar puncture in children [31]. A recent review of studies on the effectiveness of medical hypnosis for reducing procedure-related pain in children and adolescents less than 19 years old consistently found that hypnosis was more effective than control conditions in alleviating discomfort associated with bone marrow aspirations, lumbar punctures, voiding cystourethrograms, the Nuss procedure (surgery to correct congenital deformities of pectus excavatum), and post-surgical pain [32]. Furthermore, all controlled studies included in the review found the effectiveness of hypnosis to be either equal or superior to that of distraction [32].

In adults, medical hypnosis during burn wound debridement has resulted in clinically significant pain and anxiety reduction [7, 33–35]. Additionally, adult hypnotherapy has repeatedly demonstrated effectiveness in treating pain and psychological distress incurred by a number of classically uncomfortable procedures including tooth extraction [36], bone marrow aspiration [37], and colonoscopy [38].

Prior research has shown that children over the age of three respond to medical hypnosis [30, 39] and that hypnotic responsivity (historically known as “hypnotizability”) is generally greater in children than in adults [29, 39]. It has been proposed that hypnotherapy may be the preferred non-pharmacological intervention for young children, given how easily and fluidly they enter trance-like states (e.g., playing with imaginary “friends”) [29, 40]. The hypnotic induction of an altered state of consciousness in children is characterized by narrowed attention, absorption in trance phenomena, and some degree of detachment from the surrounding external environment. Hypnotic intervention provides a context in which children can exercise their curiosity while producing a novel experience which increases their mastery over physical and mental response patterns. In the younger child, play is a natural form of expression and problem-solving which uses altered levels of consciousness to vivify the child’s experience. Thus, the normally developing child has a naturally large repertoire of imaginative experience to draw on when provided with a hypnotherapeutic intervention [41]. Despite children’s generally greater responsivity to hypnotherapy compared to that of adults, to our knowledge no randomized controlled trial (RCT) has examined the effectiveness of medical hypnosis for decreasing pain intensity, healing times, procedural anxiety, and rates of traumatic stress reactions in pediatric burn patients. Together these findings, in addition to the ease of application, lack of adverse side effects, and cost-effectiveness of medical hypnosis with children [42], provide a strong rationale for implementing this study.

### Objectives

The primary aims of this study are to investigate whether medical hypnosis affects pain intensity and the rate of burn wound healing (i.e., re-epithelialization) in acutely burned children. The secondary aims are to investigate if medical hypnosis affects procedural anxiety, biological stress markers (salivary cortisol and salivary α-amylase), and the rate of PTSD symptom development. We hypothesize that use of medical hypnosis for pediatric patients with acute burns will decrease pain intensity, procedural anxiety, and biological stress markers during wound care procedures; improve wound healing times; and decrease rates of traumatic stress reactions compared to a standard care control group.

## Methods/Design

### Protocol and registration

This study has received ethical approval from the Queensland Children’s Health Services (Lady Cilento Children’s Hospital) Human Research Ethics Committee (approval number: HREC/15/QRCH/32) and the University of Queensland Ethics Committee (approval number: 2015000456). The study methodology was documented in a protocol and registered prior to starting recruitment (Australian New Zealand Clinical Trials Registry, ID: ACTRN12615000419561). This is version 1 of the study protocol completed on 10 September 2015. Methods have been documented in accordance with the Consolidated Standards of Reporting Trials (CONSORT 2010) [43] and Standard Protocol Items: Recommendations for Interventional Trials (SPIRIT 2013) [44] statements. The intervention has been described using the Template for Intervention Description and Replication (TIDieR 2014) guidelines [45].

### Design and setting

This study is a single-center, superiority, parallel-group, prospective randomized controlled trial (see Fig. 1). Eligible participants are randomized to receive either (1) medical hypnosis (intervention group) or (2) standard care (control group).

**Fig. 1 Fig1:**
[figure not shown]
Flow diagram of the trial

Participants are recruited from the Pegg Leditschke Paediatric Burns Centre (PLPBC) at Lady Cilento Children’s Hospital (LCCH), Brisbane, Australia (AUS). The PLPBC is the major specialist tertiary burns center for Queensland and Northern New South Wales, Australia. The center’s clinical multidisciplinary team treats approximately 800 new burn patients per year.

### Eligibility criteria for participants

Eligible participants are children aged between 4 and 16 years (inclusive) who meet the inclusion criteria of (1) an acute burn of any depth (excluding erythema only) and (2) presentation to the PLPBC for treatment (inpatient or outpatient). Children are excluded from the study if they are non-English speaking; cognitively impaired; under the care or investigation of the Department of Communities, Child Safety, and Disability Services; on ventilator support; or if they have initial burn wound care procedures carried out in the operating room under general anesthesia.

Patients of the PLPBC are identified by the center’s research manager, and participants’ eligibility is assessed by the nursing staff. All eligible patients presenting to the PLPBC are approached and invited to participate in this RCT by a clinical research team member not involved in their primary care. Parent (the term *parent* includes *legal guardian*) informed consent is obtained and recorded. Child consent is obtained for all children able to read and write. Verbal assent is obtained for all other eligible children.

### Interventions

Recruited participants are randomized into either (1) the intervention group: medical hypnosis or (2) the control group: standard care immediately prior to their first wound care procedure (i.e., dressing change or application, which may involve cleaning the wound) at the PLPBC:Intervention groupMedical hypnosisMedical hypnotherapy is used with this group after gathering baseline data. Hypnotic induction (i.e., the method for guiding the participant into a hypnotic trance) starts before nursing staff begin the burn wound care procedure and is maintained throughout the procedure. The hypnotic induction is adjusted for the participant’s age, understanding, and communicative capacity as per the clinician’s judgment. After the first hypnotherapy session (concurrent with the participant’s first wound care procedure), a maximum of four additional hypnotherapy sessions are provided during subsequent visits to the PLPBC for wound care procedures. The clinical judgment of the treating hypnotherapist in consultation with the burns nurses and pediatric surgeons is used to determine the total number of hypnotherapy sessions. Aside from the hypnotherapy, all other treatment is administered according to established standard care. Standard care at PLPBC includes administering oxycodone, with the dosage determined by body weight, 0.1 mg/kg orally (Mundipharma Pty. Ltd., Sydney, NSW 2000, Australia); and paracetamol, 150 mg/kg orally (Sanofi-Aventis AUS Pty. Ltd., Macquarie Park, NSW 2113, Australia).Essential elements of medical hypnosisThe medical hypnosis intervention follows five stages: establishing rapport and creating a setting of positive expectancy; slowing breathing and enhancing relaxation; providing suggestions for deepening relaxation and absorption in the hypnotic state; direct hypnotic suggestions for hypnotically induced analgesia, anesthesia, anxiolysis, and rapid healing; and alerting (i.e., bringing the participant out of the hypnotic trance) [46].MaterialsThe medical hypnosis intervention designed for the treatment purposes of this trial has been documented in a manual and can be obtained from the study’s principal investigator on request.ProceduresThis study uses two hypnotic inductions: the Favorite Stories induction [47] (for children less than 7 years old) and the Favorite Place induction [29] (for children 7 years old and older). Once trance is achieved, suggestions for hypnoanalgesia or hypnoanesthesia are given using the Switches method [29, 48] or the Glove Anesthesia method [29] (sometimes referred to as the Magic Glove in the relevant literature). Suggestions for rapid wound healing are also given, and self-hypnosis is taught to the child [29].ProviderThe medical hypnosis provider in this study is a medical student and Research Higher Degree candidate who received group training by the American Society of Clinical Hypnosis (ASCH) and individual face-to-face training with [name], M.D., FACS, ABMH, Professor of Surgery and Psychiatry at Tulane University, New Orleans, USA and former president of both the ASCH and the American Board of Medical Hypnosis.All medical hypnosis is delivered face to face in a clinical consulting room within the PLPBC, LCCH. A minimum of one session and maximum of five sessions of medical hypnosis are provided for each participant in the intervention group, concurrent with their scheduled wound care procedures. Each session lasts for the duration of the participant’s wound care procedure.Although the medical hypnosis manual is adhered to as closely as possible, the intervention is tailored to the participant based on their developmental and chronological age, capacity to focus, distress related to the total burn area and depth, acuity and nature of the burn event, and location of the burn. This adherence allows replication of hypnotherapy procedures used to the extent permitted given that the children and adolescents who participate have varied developmental and chronological ages, presentations, and levels of capacity for focus, as well as distress related to total burn area and depth, acuity and nature of the burn event, and different specific anatomy involved.Control groupStandard careStandard procedural distraction is available to this group, including music, toys, the Ditto™ (Diversionary Therapy Technologies, QLD, Australia) [6] and other electronic devices (e.g., TV, hand-held games, portable DVD players), books, and parental presence. The consulting hypnotherapist is positioned in the procedure room with the participant but does not provide hypnosis to ensure that the only difference is the use of medical hypnosis. The hypnotherapist does not interact with participants in the control group to avoid potentially using hypnotic techniques and is only present to help record outcome measures associated with wound care procedures.

### Outcomes

Previously validated scientific measures are used for all outcomes. The duration of each wound care procedure is timed. Prior to the application of new dressings at the first dressing change, the burn depth is calculated by measuring blood perfusion at the burn site using a Moor LDI2-BI2 Laser Doppler Imager (Moor Instruments Limited, Devon, UK). Data is collected at every dressing change until ≥95 % re-epithelialization occurs, and the total number of dressing changes is recorded.

#### Primary outcome measures

The two primary outcome measures are pain intensity and wound healing (i.e., re-epithelialization time). Pain measurements are taken several times for each participant. The first time point (baseline) is immediately before premedication prior to removal of the wound dressing in clinic. The second time point is immediately after the new dressing is in place; the worst pain is assessed reflecting the maximal pain intensity experienced by the participant during the procedure (retrospective). For the third time point, a final pain assessment occurs to gauge pain intensity immediately after the new dressings are in place and hypnotherapy has ceased. No pain measurements are taken during hypnosis. Assessing pain intensity in this manner effectively gives three time points relative to the procedure: before, during, and after. These measurements take place at each subsequent dressing change until ≥95 % wound re-epithelialization.

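### The third ('after') pain rating waits for an event that only the hypnosis arm has, so the two arms may be rated at different times after the dressing

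*Protocol article*

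**What the plan says.** Under Primary outcome measures, the protocol article describes three pain ratings at each dressing change.

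- **Before:** a baseline rating, taken before premedication.
- **During:** "The second time point is immediately after the new dressing is in place; the worst pain is assessed". This is a retrospective rating of the maximal pain during the procedure.
- **After:** "a final pain assessment occurs to gauge pain intensity immediately after the new dressings are in place and hypnotherapy has ceased".

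The same section adds: "No pain measurements are taken during hypnosis".

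Under Interventions, hypnotic induction "starts before nursing staff begin the burn wound care procedure and is maintained throughout the procedure". The last of the five stages is "alerting (i.e., bringing the participant out of the hypnotic trance"). The section also states: "Each session lasts for the duration of the participant’s wound care procedure". For the control arm: "The hypnotherapist does not interact with participants in the control group to avoid potentially using hypnotic techniques".

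Under Data analysis, a repeated-measures GEE with main effects of group and time is planned for pain.

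**The concern.** The rule for the third rating joins two conditions. The first, dressings in place, applies to every child. The second, hypnotherapy over, can be met only in the hypnosis arm. In timing, that second condition is all that separates the third rating from the second. The 'after' time point of a primary outcome is therefore defined partly by treatment received.

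If procedural pain eases once handling of the wound stops, a child rated some minutes later reports less pain for that reason alone. A systematic delay in one arm would then appear as a treatment effect.

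Two features make this harder to dismiss. The Blinding section accepts that hypnosis cannot be masked, and the primary investigator documents the child and parent pain scores, so the moment of rating is in the hands of unmasked staff. In addition, the article mentions timing the procedure and noting the saliva collection time, but no time for the pain rating itself. Without that time, an analysis could neither detect nor adjust for a gap.

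**Working it through.** **1. The timing rules by arm**

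| Rule (protocol article) | Hypnosis | Control |
|---|---|---|
| Second rating: new dressing in place | applies | applies |
| Third rating: new dressings in place | applies | applies |
| Third rating: hypnotherapy has ceased | applies | cannot occur; no substitute named |
| No pain rating during hypnosis | applies | has no effect |
| Hypnosis maintained throughout the procedure, ending with alerting | applies | does not apply |
| Session lasts as long as the procedure | applies | does not apply |

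The third, fourth and fifth rows together allow a later rating in the hypnosis arm: if trance is held until the dressing is finished, alerting comes at or after that point, and the rating must wait for it. The sixth row points the other way: session and procedure end at about the same time. The length of alerting, and when it starts relative to the end of the dressing, are not given. The fourth row also means that the second rating can be delayed in the hypnosis arm.

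**2. The plan's own figures (Sample size section)**

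Two-sided testing is assumed, since sidedness is not stated.

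- Healing: difference 3 days, SD 4, so effect size 3/4 = 0.75. The two-sample t-test with 80% power and α 0.05 needs 28.9, so 29 per group, as stated.
- Dropout: 29/0.90 = 32.2, so 33 per group and 66 in total, as stated.
- Pain: difference 2, SD 2.5, so effect size 2/2.5 = 0.80. This needs 25.5, so 26 per group. Power is 0.85 at 29 and 0.89 at 33 per group.

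These figures reproduce and do not depend on the timing question.

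**3. Illustration of what a timing shift would do**

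Inputs from the document: SD 2.5; 29 or 33 per arm. Assumption: no true effect, and a shift of b points at the third rating caused only by timing. Rejection rate = power of the two-sided two-sample t-test at α 0.05 with effect size b/2.5.

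| Shift b (points) | b/2.5 | 29 per arm | 33 per arm |
|---|---|---|---|
| 0 | 0 | 5.0% | 5.0% |
| 0.1 | 0.04 | 5.3% | 5.3% |
| 0.25 | 0.10 | 6.6% | 6.9% |
| 0.5 | 0.20 | 11.6% | 12.6% |
| 1.0 | 0.40 | 32.2% | 36.0% |

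**4. What shift could arise**

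The document gives neither the delay nor the fall in pain. Under an assumed exponential fall, the gap is p0 × (1 − 2^(−t/h)), where p0 is pain at dressing end, h its half-life and t the extra delay in the hypnosis arm. All three are assumptions.

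- p0 = 3, h = 30 min, t = 2 min: 0.14 points
- p0 = 5, h = 20 min, t = 5 min: 0.80 points
- p0 = 5, h = 10 min, t = 5 min: 1.46 points
- t = 0: 0 points

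**5. Dilution in the GEE**

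The rates in step 3 are for one time point. If the group main effect weighted the three ratings about equally and only the third were shifted, a shift of b would enter as about b/3: 1.0 becomes 0.33 and 0.5 becomes 0.17. If the second rating were shifted as well, the dilution would be smaller.

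**The case against.** The strongest objection is the sentence tying session length to the length of the procedure: on the document's own terms hypnosis and dressing end together, and no delay is stated anywhere. The clause about hypnotherapy ending can be read as a safeguard against rating a child in trance. This stands in so far as the gap may be close to nil. It does not remove the problem, because the clause still applies to one arm only and the document does not fix when alerting takes place.

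Several stronger readings are tempting and are not supported:

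- **That the comparison is biased towards hypnosis.** The document shows a route to bias. Its direction depends on pain falling after the procedure, and its size on a delay that is not given.
- **That the rating is timed by the end of hypnotherapy alone.** The dressing condition binds both arms.
- **That controls are rated with no delay.** The worst-pain rating, the anxiety rating, a 2-minute saliva collection and the heart rate are also due right after the dressing in both arms, in no stated order. Some delay is possible for controls too.
- **That the third rating duplicates the second in controls.** The second asks for worst pain during the procedure and the third for pain afterwards. Asked close together, they remain different questions.
- **That only the third rating is exposed.** The bar on ratings during hypnosis can delay the second as well.

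It is also fair to say that minute-level timing is often left to the full protocol or the data forms, and that the intervention manual is not shown. But the point here is not a missing detail: the article does state a rule, and that rule depends on the arm.

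**Conclusion.** The point holds as a weakness in how a primary-outcome rating is defined. The trigger for the third rating includes a condition that exists in one arm only, and following the rule as written can place the hypnosis arm's rating later than the control arm's. If pain declines after the procedure, that would favour hypnosis.

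The size cannot be determined from the document. The illustrative false-positive rate at this single time point runs from about 5% for a shift of 0.1 points to 32–36% for 1.0 point, which is half the planned difference of 2. It rests on SD 2.5, 29 to 33 per arm, no true effect and an assumed shift. The effect on the GEE group term would be smaller. A reader should not conclude that the trial's pain result is biased. The supportable conclusion is that the rule permits differential timing in an unmasked trial, and that the data collection described in the article would not show whether it occurred.

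**What to change.** Use one anchor for both arms. Take the post-dressing pain ratings, both worst pain and pain afterwards, at the same fixed number of minutes after the last dressing is secured, in a stated order. Choose an interval long enough for alerting to be complete, so that the bar on ratings during hypnosis is still respected. Remove the end of hypnotherapy as a trigger. Record the minutes from dressing end to each rating, and report them by arm.

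If recruitment has gone too far to change the timing, adding the time field for the remaining dressing changes would still allow the gap to be described.

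The cost is a sentence or two in the protocol and a time field on the form. The downside is a wait of a few minutes for control children and an 'after' rating that falls slightly later than now intended.
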